#### Quality of life

We will examine quality of life and patient experience of using the device. Quality of life will be measured using the validated questionnaires described above. On completing the intervention, participants will complete a questionnaire on compliance, comfort and usability of the device in the postoperative setting. Qualitative data and free text comments from this will also be collected.

#### Systemic inflammatory response

To monitor the inflammatory response, we will use commonly utilised postoperative inflammatory markers, namely c-reactive protein(CRP) and values derived from the full blood count and biochemistry including neutrophil-to-lymphocyte ratio (NLR) and modified Glasgow Prognostic Score (mGPS). These inflammatory markers are well-established metrics linked to both sarcopenia, myosteatosis and prognosis in colorectal cancer [29–31]. We have chosen these markers for a number of reasons; they are routinely taken and cost-effective and allow for comparison with substantial historical data. We may also require results from other trusts, due to the national spread of our patient population, and we cannot support them in obtaining non-routine tests as part of this study.

### Planned statistical analyses

This study will be performed in line with the CONSORT criteria (http://www.consort-statement.org/consort-2010). Initially outliers, patterns of attrition and missing data will be identified using a combination of graphical displays and descriptive statistics allowing decisions on the assumption of normality. The primary analysis will be of observed data only, with patients with missing data omitted from the analysis. If the primary outcome has >10% missing data points, a sensitivity analysis will be performed using multiple imputation to estimate the missing values.

Data will be analysed by a statistician blinded to the intervention. Analyses of primary and secondary endpoints will be based on the full analysis set defined according to the intention to treat principle. Safety analysis will be performed for the on all enrolled individuals with disclosure of any significant adverse events. The full analysis set consists of all participants consented and randomised with valid baseline assessments. Participants will be analysed according to the study arm they were assigned at randomisation.

The primary outcome is myosteatosis at 3–6 months post-surgery, derived from the mean muscle attenuation on CT body composition analysis. This will be analysed using analysis of covariance (ANCOVA), with muscle attenuation values at baseline used as a covariate in the analysis.

The secondary outcome measures measured on a continuous scale, and with a baseline measurement will be analysed using equivalent methods as the primary outcome. For continuous outcomes with no baseline measurement, group comparisons will be made using either the unpaired *t*-test or Mann-Whitney test, depending on data distribution. The chi-square test, or Fisher’s exact test, will be used to compare categorical outcomes between the study groups.

Significance will be assumed when *p*<0.05.

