## Background

Radical multi-visceral resection of pelvic tumours, known as pelvic exenteration, is being utilised to successfully treat a number of intra-abdominal malignancies [1]. Pelvic exenteration for locally recurrent (LRRC) or primary advanced rectal cancer has a high morbidity and mortality. The *PelvEx Collaborative* analysed data from 1184 patients, who underwent surgery for LRRC, and found that 2% of patients died within 30 days of surgery and 32% of patients experienced a major complication [2]. Despite this high morbidity and mortality, these complex procedures are increasingly practised in specialist centres. Following surgery, these patients enter a catabolic crisis where incapacitation and high protein and fat metabolism lead to a marked loss in skeletal muscle [3–5]. Low skeletal muscle mass (sarcopenia) and fatty infiltration (myosteatosis) are independently associated with poorer post-operative outcomes following surgery for colorectal cancer [6, 7]. The aetiology behind sarcopenia and myosteatosis is complex and multifactorial and includes inflammatory changes, hormonal changes, loss of function, fatigue and energy balance [8]. However, strategies to preserve skeletal muscle mass, quality and function may improve these outcomes.

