	Pain/discomfort and anxiety/depression			
Quality of life (colorectal specific)	EORTC QLQ - CR29 Function and Symptoms	4 multi-item scales and 19 single items assessing common symptoms and problems in colorectal cancer	Change in score between events	Pre-surgery, 6 and 12 months post-surgery
Function	Berg Balance Scale (BBS)	Berg balance score (0–56)	Change in BBS score	Pre-surgery and 6 months post-surgery
	30 s sit to stand	Number of full sit-to stand actions completed in 30 s	Change in number of successful actions	
	6-min walk test	Distance walked in 6 minutes	Change in metres	
Thigh circumference	Thigh circumference, 5cm above the superior pole of the patella	Circumference in cm	Change in thigh circumference between groups	
Dose response to NMES	Pre- and post-operative mean muscle attenuation (L3) (MMA) and hours of device usage	Change in MMA/time	Linear regression	3–6 months post-surgery
Patient satisfaction	Free text responses and satisfaction scores derived from each domain (see patient satisfaction survey supplementary material).	Qualitative and visual analogue scale 1-10	Qualitative responses Median score between groups on each domain assessed	8 weeks post-surgery
Bioimpedance analysis	Phase angle = (Xc/R)*180°/π	Cellular resistance (R) and cellular reactance (Xc)	Change in phase angle at each time point	Baseline, day 2 post operatively, day 28 postoperatively (if in hospital), day of discharge, first post-operative follow-up appointment

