#### Functional assessment

It is important that we measure not only the anatomical effects of NMES, i.e. increased muscle mass on CT and anthropometric changes, but we identify whether these patients demonstrate both a functional and physiological improvement. To that end, we will assess functionality preoperatively at diagnosis and post-operatively at 3 months using the validated instruments of the 6-min walk test [24], 30 s sit-to-stand test [23] and Berg Balance scale (BBS) [21, 22]. These assessments will be undertaken in the complex cancer clinic by either a specialist physiotherapist or research fellow. These data will be treated as continuous outcome variables with the exception of BBS which will be categorical.

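### The observed-data rule, as it carries over to the 6-minute walk and sit-to-stand, drops patients who die or are too disabled to be tested, which can bias the functional comparison in either direction

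*Protocol article*

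**What the plan says.** In the protocol article, Planned statistical analyses, the rule for missing data is: "The primary analysis will be of observed data only, with patients with missing data omitted from the analysis". One sensitivity analysis follows: "If the primary outcome has >10% missing data points, a sensitivity analysis will be performed using multiple imputation to estimate the missing values". Secondary outcomes on a continuous scale with a baseline value "will be analysed using equivalent methods as the primary outcome"; categorical outcomes go to chi-square or Fisher's exact test. The same section promises: "Analyses of primary and secondary endpoints will be based on the full analysis set defined according to the intention to treat principle".

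Functional assessment says of the 6-minute walk, sit-to-stand and Berg tests: "These assessments will be undertaken in the complex cancer clinic by either a specialist physiotherapist or research fellow". On data type it says: "These data will be treated as continuous outcome variables with the exception of BBS which will be categorical". Table 2 defines the walk only as "Distance walked in 6 minutes", sit-to-stand as a count of completed actions, and Berg as a score from 0 to 56.

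Sample size estimation accepts that loss on secondary outcomes may exceed the 5% assumed for the primary outcome, and makes no allowance for it. Table 2 places the function tests at 6 months; Data collection and Functional assessment place them at 3 months.

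**The concern.** The article justifies a low dropout rate by the primary outcome coming from routine CT scans. That reasoning does not extend to a performance test that requires the patient to come to clinic and make the attempt. A patient who misses it through death, a continuing complication or disability probably has a poor functional outcome, so the gap is not random.

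The article itself gives grounds to expect such patients. Its Background cites a cohort operated on for recurrent disease in which 2% died within 30 days and "32% of patients experienced a major complication". Its Discussion describes limited mobility from pain and disability after this surgery.

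Functional assessment uses these tests to ask whether a change in muscle is matched by a functional gain, and the trial is meant to guide phase 3. If the arms differ in how many poor performers are lost, the observed-data comparison is no longer between the randomised groups, whatever the analysis set is called.

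**Working it through.** **1. Which tests the rule reaches.**

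| Test | Data type (Functional assessment) | Analysis line that applies | Does the omission rule reach it? |
|---|---|---|---|
| 6-minute walk | continuous, with baseline | equivalent methods to the primary | yes, by extension |
| 30 s sit-to-stand | continuous, with baseline | equivalent methods to the primary | yes, by extension |
| Berg | categorical | chi-square or Fisher | not expressly |

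A patient who attends and completes no stand can score 0, and Berg also starts at 0. The patients without a value are those who died, those who could not attend, and those for whom the walk was not attempted.

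**2. The plan's own figure.** Adjusted SD = 9.4 × √(1 − 0.3²) = 8.967 HU. Then n = 2 × (1.960 + 1.282)² × (8.967/8)² ≈ 26.4, so 27 per group and 54 in total. 54/0.95 = 56.8, rounded up to 57 and then to an even 58. The stated figures reproduce. They concern muscle attenuation only; no figure is given for function.

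**3. Direction and size under a common threshold.** Assumptions, none from the documents: functional score normal with SD 1, true benefit d, and a patient in either arm untestable below the same cut-off c, set so that a share p of sham patients falls below it. The mean of a standard normal above c is m(c) = φ(c)/(1 − Φ(c)). Without baseline adjustment, the observed difference is d + m(c − d) − m(c). For d = 0.8:

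| p in sham | c | m(c − 0.8) | m(c) | Observed difference |
|---|---|---|---|---|
| 5% | −1.645 | 0.020 | 0.109 | 0.71 |
| 10% | −1.282 | 0.047 | 0.195 | 0.65 |
| 20% | −0.842 | 0.109 | 0.350 | 0.56 |
| 32% | −0.468 | 0.199 | 0.526 | 0.47 |

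**4. With baseline adjustment at the trial's size.** Simulation with 29 per arm and baseline correlation 0.3 (borrowed from the muscle attenuation assumption), true benefit 0.8 SD:

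| p in sham | ANCOVA estimate, observed only | Power, observed only | Power, baseline-adjusted worst rank |
|---|---|---|---|
| 5% | 0.72 | 83% | about 85–86% |
| 10% | 0.67 | 78% | about 85–86% |
| 20% | 0.57 | 67% | about 85–86% |
| 32% | 0.50 | 57% | about 85–86% |

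Type I error of the rank analysis is near 5%. A repeat run agreed to within about 0.01 SD and one to two percentage points.

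**5. Other patterns of loss.** Observed-data ANCOVA in very large samples, correlation 0.3:

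| Pattern | True effect | Estimate |
|---|---|---|
| Common threshold, 5/10/20/30% of sham untestable | 0.5 | 0.44 / 0.40 / 0.34 / 0.29 |
| Common threshold, same shares | 0 | 0.00 throughout |
| Lowest 15% lost in each arm | 0.5 | 0.50 |
| Lowest 10% lost in sham; 15/20/30% in NMES | 0 | 0.07 / 0.15 / 0.29 |
| Lowest 10% lost in sham; 15/20/30% in NMES | 0.5 | 0.58 / 0.64 / 0.78 |

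A true 0.5 SD is thus shrunk by 12% to 41%, left alone, or inflated by 15% to 57%, depending on which patients are missing. By symmetry, a true harm under a common threshold is shrunk towards zero.

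**The case against.** The strongest reply is that this is detail an article leaves to the full protocol or the analysis plan. That answers the lack of a score for untestable patients, and such a rule may exist elsewhere. It does not fully answer the point, because the article states an omission rule and carries its methods to these outcomes.

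A second reply is that the omission sentence concerns the primary analysis and that equivalent methods may mean only ANCOVA with a baseline covariate. That reading is possible. But then the article names no handling for function while promising an intention-to-treat analysis set, and the imputation analysis still covers the primary outcome alone. Imputation that assumes data missing at random would not recover patients missing because they are disabled.

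Several stronger readings are tempting and not supported:

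- A reader might infer that the comparison must understate any benefit. That needs a common threshold and a real NMES benefit. Nothing in the document says which arm will lose more low performers.
- A reader might infer that nobody who fails a test gets a score. An attending patient can score 0.
- A reader might take Berg to fall under the omission rule. It is categorical and reached only indirectly.
- A reader might take 32% as the untestable share. It is a complication rate from a recurrent-cancer cohort, while this trial also enrols primary disease and the Discussion expects recovery to baseline or beyond. Here it serves only as the top of an assumed range.

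It is also fair that these are secondary outcomes on which the trial was not powered, that some non-attendance may be unrelated to function given the national spread of patients, and that worst-rank scoring changes the question asked. That last point argues for adding such an analysis, not for replacing the ANCOVA.

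**Conclusion.** The concern holds in a limited form. For the 6-minute walk and sit-to-stand, the observed-data rule as carried over omits patients who died or were physically unable to attend or attempt the test, and no stated sensitivity analysis addresses this. The bias can run in either direction.

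Its size is unknown because the article gives no untestable share and no functional effect size. Under the assumed common threshold, with 5% to 32% of sham patients untestable and a true benefit of 0.8 SD, the baseline-adjusted estimate falls to between 0.72 and 0.50 SD. At 5% the cost in power is two to three percentage points, which is minor. The primary outcome and the sample size of 58 are not affected.

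**What to change.** - Record on the CRF, for each function test not done, whether the reason was death or physical inability, or something unrelated such as travel or scheduling. Without this the two kinds of absence may not be separable later.
- Pre-specify an added rank analysis of the walk and sit-to-stand, adjusted for the baseline score, that gives death or physical inability the worst rank. Report it beside the observed-data ANCOVA. Tests missed for unrelated reasons stay omitted or are imputed.
- For Berg, apply the matching rule by placing such patients in the worst category.
- Reconcile the timing of the function tests between Table 2 (6 months) and Data collection and Functional assessment (3 months), since the share of untestable patients depends on it.

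The cost is one CRF field and a few lines of analysis text, with no extra patients or visits. The downside is that the added result is a rank comparison that combines death with disability; the ANCOVA still supplies the difference in metres or stands.

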### Adverse event reporting

Adverse event reporting in this trial is carried out in accordance with the NHS Health Regulation Authority (HRA). All serious adverse events (SAE), whether or not related to participation in the trial, will be reported immediately to the trial sponsor; these will be reviewed by the trial sponsor and should further investigation be required the trial sponsor may pause the trial to carry out investigation. Should a SAE occur as a direct result of the trial device or as a direct result of participation in the trial the trial will be paused and a non-CTIMP safety report form will be submitted to the relevant research and ethics committee with 15 days of the Chief Investigator becoming aware of the event. In this instance, the SAE report will be unblinded as required by the HRA. Patient-reported adverse events deemed expected or non-serious will be reported in the final publications arising from this trial, we expect many of these minor events to be reported in the patient satisfaction questionnaire.

## Discussion

Patients who undergo major pelvic surgery have limited mobility due to postoperative pain and disability. These patients are therefore at much greater risk of suffering from muscle wasting than patients undergoing more routine colorectal surgery. This is a result of greater loss of function, greater immobility and potentially a more profound immunogenic inflammatory response.

Currently, these patients receive postoperative physiotherapy; due to limited time, postoperative pain, patient choice and resource availability, it is unlikely that the patients are exercised to their full potential. A prescribed programme with a NMES device would allow patients to choose when they undertake muscle stimulation exercise for example once they had received adequate analgesia or at a time convenient to them. This would hopefully improve compliance and bring about a hypertrophic response in the muscle.

We know that in muscle disuse in healthy individuals NMES may provide an effective treatment to preserve muscle volume [16]. Maddocks’ work in cancer patients [13, 19] however did not demonstrate a significant increase in muscle volume and therefore one may question the rationale behind use in this patient group (these differences are summarised in Table 1). The cancer population in these studies is different from our own in a number of respects beyond the diagnosis alone and as such we may find NMES to be a more suitable intervention in our patient group. Maddocks’ work was performed in a palliative population with active cancer whilst postoperatively our patients will be theoretically cancer free with perhaps a few exceptions in patients who have solitary metastases (which, by the criteria of inclusion, are amenable to curative treatment). In view of their palliative status, Maddocks’ population would be expected to decline in health over time whilst our population would be expected to make a recovery up to or even beyond their preoperative state and therefore NMES may increase the rate of or facilitate this recovery. Our population is confined to bed rest for over a week’s duration following surgery and therefore activity provided by NMES may help arrest the muscle loss associated with disuse as in Hasegawa’s population whose anterior cruciate ligament repair cohort was subject to muscle loss through disuse rather than disease [16]. Finally, our patients will receive intensive inpatient support by the ward physiotherapists and the research team; they will receive positive reinforcement of their use of the device and will be asked to complete an exercise diary which the physiotherapy team, will review with them at each point they receive formal physiotherapy sessions. This level of direct input and positive reinforcement is notably more than in the previous NMES studies of Maddocks’ and therefore we would hope compliance and correct usage would be increased.

The inflammatory effects of exercise are known to be paradoxical in that exercise drives both a pro and anti-inflammatory response [32, 33]. We propose that the metabolic result of exercise in cancer patients will drive a beneficial anti-inflammatory response. This immunomodulation may in part help support the body’s immune system in the early stages of post-surgical recovery and as such may potentially support the cellular immune system in being able to identify and destroy malignant cells shed at the time of surgery.

In our patient group, NMES will potentially allow a higher degree of exercise than the patients would otherwise be able to undertake due to their incapacity. Our hope is that this promotes muscle preservation, allowing earlier mobilisation and a more expedient return to “normal” exercise and function, further reinforcing the preservation of muscle mass. Increased muscle mass and quality are associated with improved long-term outcome such as disease-free survival [6] we intend to follow our cohort for 5 years to see if NMES provides evidence to support improvement in these oncological outcomes through muscle preservation.

## Summary

Exercise in healthy individuals leads to increased muscle mass; exercise can bring about an anti-inflammatory effect due to muscle physiology thus obfuscating a key pathway driving secondary sarcopenia. Preservation of muscle mass through early post-operative intervention with NMES would allow a more rapid return to normal exercise and normal function leading to greater muscle preservation and subsequently improved outcomes.

### Trial status

BiCyCLE NMES is currently recruiting patients; recruitment began on the 31 May 2019 and is expected to be completed by March 2021. Protocol version 6 dated 05/06/20 is currently approved by the research ethics committee and the HRA.

## Data Availability

Access to the final trial data set will be available to the trial team, the sponsor and for review by the independent data monitoring committee appointed by the sponsor.
